## Abstract

Patellofemoral pain (PFP) is one of the most prevalent injuries in runners. Unfortunately, a substantial part of injured athletes do not recover fully from PFP in the long-term. Although previous studies have shown positive effects of gait retraining in this condition, retraining protocols often lack clinical applicability because they are time-consuming, costly for patients and require a treadmill. The primary objective of this study will be to compare the effects of two different two-week partially supervised gait retraining programs, with a control intervention; on pain, function and lower limb kinematics of runners with PFP. It will be a single-blind randomized clinical trial with six-month follow-up. The study will be composed of three groups: a group focusing on impact (group A), a group focusing on cadence (group B), and a control group that will not perform any intervention (group C). The primary outcome measure will be pain assessed using the Visual Analog Pain scale during running. Secondary outcomes will include pain during daily activities (usual), symptoms assessed using the Patellofemoral Disorders Scale and lower limb running kinematics in the frontal (contralateral pelvic drop; hip adduction) and sagittal planes (foot inclination; tibia inclination; ankle dorsiflexion; knee flexion) assessed using the MyoResearch 3.14—MyoVideo (Noraxon U.S.A. Inc.). The study outcomes will be evaluated before (t0), immediately after (t2), and six months (t24) after starting the protocol. Our hypothesis is that both partially supervised gait retraining programs will be more effective in reducing pain, improving symptoms, and modifying lower limb kinematics during running compared with the control group, and that the positive effects from these programs will persist for six months. Also, we believe that one gait retraining group will not be superior to the other. Results from this study will help improve care in runners with PFP, while maximizing clinical applicability as well as time and cost-effectiveness.

## Introduction

Millions of people practice running, an activity that requires minimal equipment and benefits cardiac, metabolic, and mental health. However, running tends to cause high injury rates (19% to 92%) leading to social and economic losses [1–5]. In runners, the knee is the main site affected (7.2% to 50%) [5] and one of the main injuries is patellofemoral pain (PFP) (5.5%) [6]. Unfortunately, 55% of treated individuals present unfavourable recovery at three months and 40% at twelve months [7]. Also, 57% do not recover completely in five to eight years [8].

Various interventions are recommended for the treatment of individuals with PFP, among which gait retraining can be highlighted [9]. A systematic review by Agresta and Brown [10], demonstrated immediate and short-term effects (1 and 3 months) on pain, function, and biomechanics of individuals with PFP, results corroborated by Barton and colleagues [11], who associated current evidence with expert opinions. Findings were also outlined by critical reviews conducted by Jeon and Thomas [12] and Davis and colleagues [13].

However, the evidence of the benefits of gait retraining comes mainly from case series and quasi-experimental studies that did not have a control group and did not report adverse effects or limiting factors for this intervention [10–12]. The need for high-quality evidence justifies conducting clinical trials that show the effects of gait retraining programs in individuals with PFP.

The systematic review and meta-analysis of Neal and colleagues [14], found moderate evidence that runners with PFP had increased hip adduction and contralateral pelvic drop, based on cross-sectional studies. Reducing peak knee flexion could also be an important variable to address in runners with PFP, given that greater flexion has been associated with greater patellofemoral joint loading [15]. Increasing running cadence has been shown to be effective in reducing hip adduction [16,17], contralateral pelvic drop [16], and knee flexion [16,17] in subjects with PFP. Three additional studies show that increasing cadence reduces compression forces in the patellofemoral joint [15,18,19]. Another strategy with interesting results is modifying knee joint loading through visual and verbal feedback on impact. Indeed, two studies found reductions in ground reaction force loading rates using specific cues on “run softer” and an accelerometer [20,21], and this has been shown to reduce the incidence of PFP [22].

Unfortunately, the main gait retraining protocols are not feasible in clinical practice, since they consume a lot of time and financial resources for patients [11,23]. In fact, a recent study showed positive effects after a single session of cadence retraining on symptoms and biomechanics of runners with PFP [16]. Therefore, we chose to compare two partially supervised running retraining programs, one group focusing on impact and another group focusing on cadence.

The primary objective of the study will be to compare the effects of two different two-week partially supervised gait retraining programs, one focusing on impact and the other focusing on cadence, with a control intervention; on pain, function and lower limb kinematics of runners with PFP. The secondary objective of the study will be to compare the effects of these programs on pain, function and lower limb kinematics six months after their application.

Gait retraining with focus on impact has been proved to modify the ground reaction forces in pain free-subjects (tibial acceleration, vertical impact peak, instantaneous and average loading rates) [20–22], while the gait retraining with focus on cadence has been proved to modify symptoms, kinematic (increased hip adduction, contralateral pelvic drop and knee flexion) and kinetic aspects (patellofemoral loading rate) in patellofemoral pain patients [15,16]. Our hypothesis is that the two partially supervised gait retraining programs will be more effective in reducing pain, improving symptoms, and modifying lower limb kinematics during running compared with the control group, and that the positive effects from these programs will persist for six months. It is expected a reduction in contralateral pelvic drop, hip adduction, knee flexion, ankle dorsiflexion, tibia and foot inclination in both retraining groups. Also, we believe that one gait retraining group will not be superior to the other. The main motivations to perform a comparison of partially supervised gait retraining programs are the lack of clinical trials and the possibility to provide viable options for runners with PFP.

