## Methods

### Study design

This will be a randomized, single-blind, parallel group, three-arm superiority clinical trial, using a 1:1:1 allocation rate and six-month follow-up. The three arms of the study will be composed of three groups: a group that will perform partially supervised gait retraining with a focus on impact (group A), a group that will perform partially supervised gait retraining focusing on cadence (group B), and a control group that will not perform any intervention (group C). The study outcomes will be evaluated before (t0), immediately after (t2), and six months (t24) after starting the protocol. The study will be carried out at the Instituto Trata located in the city of Goiânia, Goiás, Brazil. This protocol was written in accordance with the SPIRIT (Standard Protocol Items: Recommendations for Intervention Trials) (S1 and S5 Files) and the results will be reported in accordance with the CONSORT (Consolidated Standards Of Reporting Trials). Information regarding the dissemination of the results can be found in S2 File.

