### Sample size

An a priori sample size calculation was conducted using the eta-partial square value of the group-by-time interaction for worst knee pain (0.19) obtained in a previous study that compared the effects of three gait retraining programs on runners with patellofemoral pain [27]. In G*Power software [28], we used ANOVA: repeated measures, within-between interaction, with the following parameters: effect size f = 0.48 (obtained through eta-partial square value); level of confidence = 0.05; power = 99%; number of groups = 3; number of measurements = 3. The total sample size obtained was 21 participants, however, to account for losses during the follow-up period, the final sample size will be 30 participants.

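### The stated expectation that neither retraining program is superior to the other has no planned analysis that could support it, and a non-significant A-versus-B result is likely unless the true difference is large

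*Protocol article*

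**What the plan says.** The Abstract and the Introduction both put the expectation directly after the hypothesis that each program beats control: "Also, we believe that one gait retraining group will not be superior to the other".

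The rest of the plan is built for a different question:

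- **Framework.** Methods, Study design, describes a "three-arm superiority clinical trial, using a 1:1:1 allocation rate and six-month follow-up".
- **Sample size.** The only calculation is for "ANOVA: repeated measures, within-between interaction", with "effect size f = 0.48 (obtained through eta-partial square value); level of confidence = 0.05; power = 99"% and "number of groups = 3; number of measurements = 3". The effect is the "eta-partial square value of the group-by-time interaction for worst knee pain (0.19"), taken from "a previous study that compared the effects of three gait retraining programs on runners with patellofemoral pain". The result is 21 participants, raised to 30 for losses, so 7 to 10 per arm.
- **Analysis.** Data analysis plans a 3-by-3 mixed ANOVA, or generalized estimating equations for non-parametric data, at a 0.05 significance level with Sidak pairwise comparisons.

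The protocol gives no equivalence or non-inferiority margin, no confidence-interval criterion and no power for A versus B.

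**The concern.** A superiority test can reject equality but cannot establish it. The only planned result that could look like support for the expectation is a non-significant A-versus-B comparison. With 7 to 10 runners per arm that result is likely if the programs are alike, and also likely if they differ by a moderate amount, so it says little about which is true.

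The Introduction gives viable options for runners as a reason for comparing the programs. If the final report cites a non-significant comparison as bearing out the expectation, readers may take the programs to be interchangeable on evidence that reflects mainly the size of the trial.

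**Working it through.** **1. Reproduce the stated sample size.** Inputs from Sample size: f = 0.48, alpha 0.05, k = 3 groups, m = 3 measurements. The within-person correlation ρ and the sphericity correction are not stated; I assume ρ = 0.5 and no correction.

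- Effect size: f = √(0.19/0.81) = 0.484, as stated after rounding.
- λ = f²·N·m/(1−ρ) = 0.48² × 21 × 3/0.5 = 29.03.
- df = (k−1)(m−1) = 4 and (N−k)(m−1) = 36.
- Power = 0.990 at N = 21. The stated 21 reproduces. At N = 30 power is 0.9997.

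**2. What that power covers.** Suppose A and B are equal, ρ = 0.5, and D is the retraining-versus-control difference in change from baseline to the mean of the two follow-ups. The variance of that change is (1−ρ)(1+½) = 0.75 SD². Then D²/[0.75 × (1/14 + 1/7)] = 29.03 gives D = 2.16 SD. The omnibus test can therefore reach 99% power with no A-versus-B difference at all, and its power gives no assurance about that contrast.

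**3. Power for A versus B on the change from baseline.** Three pairs give a Sidak level of 1 − 0.95^(1/3) = 0.01695, two-sided. Per arm n = 10. Error is pooled over three arms, so df = 3n − 3 = 27 and the critical t is 2.545. SD of change = SD·√(2(1−ρ)), and the noncentrality is the true difference divided by (SD of change × √(2/n)). The protocol gives no SD for the 0–10 pain scale; SD = 2 is assumed, with ρ from 0.3 to 0.7.

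| Assumed ρ | SD of change (in SD) | Power, 1 point (0.5 SD) | Power, 2 points (1.0 SD) | Difference at which power reaches 50% |
|---|---|---|---|---|
| 0.3 | 1.18 | 7% | 28% | 1.34 SD |
| 0.5 | 1.00 | 9% | 39% | 1.13 SD |
| 0.7 | 0.77 | 15% | 64% | 0.88 SD |

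Below the last column's value, a non-significant result is the likelier outcome. At SD 2 those values are 2.7, 2.3 and 1.8 points. With 7 per arm (df = 18), power is 5–10% for 1 point and 18–44% for 2 points.

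**4. Sensitivity to the SD.** For a single-time two-sample comparison (n = 10, df = 18, Sidak level), power for a 2-point difference is 64%, 37% and 23% at SD 1.5, 2 and 2.5. For 1 point it is 16%, 9% and 6%.

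**5. Precision.** For the single-time comparison, half-width = t(df = 2n − 2) × SD × √(2/n).

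| n per arm | 95%, in SD | Sidak level, in SD | 95%, points at SD 1.5–2.5 | Sidak level, points at SD 1.5–2.5 |
|---|---|---|---|---|
| 10 | 0.94 | 1.18 | 1.41–2.35 | 1.76–2.94 |
| 7 | 1.16 | 1.48 | 1.75–2.91 | 2.22–3.70 |

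**6. What an equivalence test would need.** By two one-sided tests at 0.05, 80% power, true difference zero and SD 2, the number per arm is 69, 31 and 18 for assumed margins of 1, 1.5 and 2 points. With 10 per arm, power is about 0.1%, 8% and 39%. The margins are illustrations only; the protocol names none.

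**The case against.** The sentence is worded as a belief, follows a separate sentence that states the hypothesis, and announces no equivalence test. The primary objective compares the two programs with control, for which a superiority design is suitable, and viable options need only that each program beats control. Data analysis does not say how a non-significant A-versus-B result will be read, and an article may leave such rules to the full plan.

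Much of this stands. Two stronger readings are tempting, and the document supports neither:

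- **That the plan treats a p-value above 0.05 as confirming equivalence.** A reader might infer this and call the complement of power a rate of wrong declarations. No such rule is written, so these are rates of missed differences only.
- **That a non-significant result is likely whatever the truth.** This fails for large differences. Power for 2 points is 64% at SD 1.5 in the single-time comparison, and 64% at SD 2 with ρ = 0.7 on the change score. A gap of about 1.6 SD would be found with 80% power at the Sidak level in the single-time comparison with 10 per arm.

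What the objection does not remove is that the article itself states the expectation, twice, and itself states the framework, the sizing and the test. The mismatch lies between things it says, not in detail left out. The 99% power does not answer it either, because it belongs to the omnibus interaction at a very large effect.

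**Conclusion.** The concern holds in limited form. No planned analysis can support the expectation about A and B. At the Sidak level with 10 per arm, a non-significant result is the likelier outcome for true differences up to about 0.9 to 1.3 SD. At an assumed SD of 2, about 85–93% of 1-point differences and 36–72% of 2-point differences would be missed.

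The SD and the correlation are assumptions, so the exact percentages should not be pressed. Power for a 1-point difference stays at 16% or below in every case shown. The comparisons with control and the choice of a superiority design are not called into question. The point should be addressed, because the correction is only wording and it guards against an unsound conclusion.

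**What to change.** Restate the expectation in the Abstract and Introduction as an estimation aim, and add matching text to Data analysis. Suggested wording:

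> The difference between the impact and cadence programs will be estimated and reported with a confidence interval at the same multiplicity-adjusted level as the pairwise test. A non-significant difference will not be interpreted as similarity. Similarity will be concluded only if the whole interval lies within a margin on the pain scale that is justified and fixed before the data are seen.

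Do not write a fixed expected half-width into the plan. If one is given, label it as assumption-based: about 1.4 to 2.9 points unadjusted, or 1.8 to 3.7 at the Sidak level, for SD 1.5 to 2.5 and 7 to 10 per arm in a single-time comparison.

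The cost is a few sentences, with no change to design, sample size or treatment. The trial gives up a claim of similarity that it could not have supported.

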## Methods

### Study design

This will be a randomized, single-blind, parallel group, three-arm superiority clinical trial, using a 1:1:1 allocation rate and six-month follow-up. The three arms of the study will be composed of three groups: a group that will perform partially supervised gait retraining with a focus on impact (group A), a group that will perform partially supervised gait retraining focusing on cadence (group B), and a control group that will not perform any intervention (group C). The study outcomes will be evaluated before (t0), immediately after (t2), and six months (t24) after starting the protocol. The study will be carried out at the Instituto Trata located in the city of Goiânia, Goiás, Brazil. This protocol was written in accordance with the SPIRIT (Standard Protocol Items: Recommendations for Intervention Trials) (S1 and S5 Files) and the results will be reported in accordance with the CONSORT (Consolidated Standards Of Reporting Trials). Information regarding the dissemination of the results can be found in S2 File.

### Participants

The eligibility criteria will be: Inclusion–(I) rearfoot striking runners with cadence under 170 steps/minute; (II) age between 18 and 45 years; (III) pain around or behind the patella, with intensity of at least 3/10 on the Visual Analogue Scale (VAS), during running and one task among squatting, climbing, and descending steps, kneeling and extending the knee with resistance [24]; (IV) being comfortable running at a speed of 10–12 km/hour. Exclusion—(I) Other disorders in the lower limbs; (II) history of surgery in the lower limbs in the last year; (III) not showing interest to adhere to a strict running retraining protocol for 2 weeks. Participants with unilateral or bilateral symptoms will be included, however, in the second case, only the worst knee (pain intensity) will be considered for analysis. The participants will be recruited through contact via e-mail, telephone, and through personnel with Goiânia’s running clubs in search of runners with PFP. In this first contact, general (gender, age, body mass, height, body mass index, history of injury and previous surgeries in the lower limbs), running (experience, volume, frequency) and pain information (intensity, location, duration of symptoms and functional tasks related to pain) will be assessed to see if the participants are eligible. Based on pain information, the diagnostic will be established using the following criteria: pain around or behind the patella during functional activities that loads the patellofemoral joint [24]. A systematic review of reviews concluded that anterior knee pain produced by functional tasks is currently the best diagnostic indicator of PFP [25]. Also, PFP is evident in 80% of the people who present anterior knee pain during a squatting manoeuvre [26].

Ethics approval was obtained from the Institutional Review Board of University of Brasilia/Faculty of Ceilândia (4.132.491), and all subjects will sign a detailed consent form before entering the study (S2–S4 Files). This study was registered in the Brazilian Registry of Clinical Trials (RBR-8yb47v) (S6 File).

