### Data collection

Pain will be assessed using the Visual Analog Pain Scale [29], which consists of a numerical scale from 0 to 10 points, where 0 means no pain and 10 means the maximum pain ever experienced. Pain during daily activities (usual) and running will be measured. VAS is a reliable and valid scale for patients with PFP [30]. Function will be assessed using the Patellofemoral Disorders Scale [31], which contains 13 questions that assess the severity of symptoms and limitations in different activities related to PFP. It presents a score between 0 to 100 points where the lower the score the worse the function. The Patellofemoral Disorders Scale is a reliable and valid scale for patients with PFP, which has been translated into Portuguese [30,31]. The kinematics of the lower limbs will be assessed through digital videos using two webcams (MyoVideo 139 HD Color Webcam) sampling at 30 frames per second and two leds (LED Floodlight) [32]. Reflective markers will be placed on the manubrium sterni and bilateral on the anterior superior iliac spine (ASIS), greater trochanter, lateral femoral epicondyle, fibular head and lateral malleolus [33]. All participants will be instructed to run at 10–12 km/hour on a motorized treadmill (Movement XL 1600). A treadmill acclimatization period of 6 min will be used before running kinematics are measured [34]. The frontal plane camera will be placed on a portable tripod perpendicular to the frontal plane at a height of 1.30m and a distance of 2.55m from the treadmill. The sagittal plane camera will be placed on a portable tripod, perpendicular to the sagittal plane at a height of 1.15m and a distance of 2.50m from the treadmill. The video recordings will be analyzed using the software MyoResearch 3.14—MyoVideo (Noraxon U.S.A. Inc.). In the frontal plane the angles assessed will be: contralateral pelvic drop; hip adduction [33,35,36]. These angles will be evaluated during midstance. In the sagittal plane the angles assessed will be: foot inclination; tibia inclination; ankle dorsiflexion; knee flexion [33,37,38]. Foot and tibia inclination will be evaluated during initial contact while ankle dorsiflexion and knee flexion during midstance. In the frontal plane, the deepest landing position (near midstance) will be determined visually by slowly advancing the video frame by frame [33,37,38]. Since the cameras are synchronized this position will also be used to determine the midstance in the sagittal plane. Initial contact will be determined visually by slowly advancing the video frame by frame, and will be defined as the first time that the foot touched the ground [37]. To analyze the proposed angles, seven steps will be considered [33]. The study of Dingenen and colleagues [39] has found excellent inter-rater reliability (ICC) for all angles with ICC’s ranging from 0.93 to 0.99.

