### Outcomes measures (dependent variables)

The primary outcome of the study will be: (I) pain during daily activities (usual)—assessed using the Visual Analog Pain Scale [29]; The secondary outcomes will be: (II) pain during running—assessed using the Visual Analog Pain Scale [29]; (III) function—assessed using the Patellofemoral Disorders Scale [31]; (IV) kinematics of the lower limbs in the frontal (contralateral pelvic drop; hip adduction) [33,35,36] and sagittal planes (foot inclination; tibia inclination; ankle dorsiflexion; knee flexion) [33,37,38]–assessed through digital videos using two webcams (MyoVideo 139 HD Color Webcam) sampling at 30 frames per second and two leds (LED Floodlight) [33]. The video recordings will be analyzed using the MyoResearch 3.14 –MyoVideo software (Noraxon U.S.A. Inc.). The kinematic variables of interest were chosen based on previous studies [14,15,19,47,48]. The systematic review and meta-analysis of Neal and colleagues [14] shows a relationship between increased hip adduction and contralateral pelvic drop with PFP. The study of Wille and colleagues [47] showed that foot inclination angle and peak of knee flexion are variables that may predict knee joint loading and PFJ forces during running. Tibia inclination during initial contact is related with cadence and length [48] and these are associated with PFJ forces [18,19]. For the comparison of the three study subgroups, the average of points on the visual analog scale of pain, average of points on the scale of Patellofemoral disorders and the peak in degrees of the contralateral pelvic drop, hip adduction, knee flexion and ankle dorsiflexion during midstance and foot inclination and tibia inclination during the initial contact will be considered. The three groups will be compared before (t0), immediately after (t2) and six months (t24) after starting the protocol.

Regarding the retention of the participants, to ensure that there are minimal losses during the follow-up period, the researchers will make a monthly phone call to monitor pain, the current level of training, physical activity practice and if the participants sought for other methods of treatment. Participants can withdraw from the study for any reason at any time, in which case the researchers will collect the pain and function outcomes using the aforementioned instruments (if possible) and report the reasons why these patients did not complete the follow-up (Fig 1).

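### If usual daily-activity pain is the primary outcome, the 3/10 entry minimum does not cover it, so runners who score 0 on it can enter and cannot show a reduction

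*Protocol article*

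**What the plan says.** All references are to the Protocol article.

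- **Participants.** Criterion III requires patellar pain "with intensity of at least 3/10 on the Visual Analogue Scale (VAS), during running and one task among squatting", with steps, kneeling and resisted knee extension as the other qualifying tasks. Pain intensity is among the items collected at the first contact to judge eligibility, and that contact may be by e-mail or telephone. No inclusion or exclusion criterion refers to usual pain.
- **Data collection.** Two separate scores are planned: "Pain during daily activities (usual) and running will be measured". The scale is "a numerical scale from 0 to 10 points, where 0 means no pain and 10 means the maximum pain ever experienced".
- **Outcomes measures.** "The primary outcome of the study will be: (I) pain during daily activities (usual". Running pain comes second: "The secondary outcomes will be: (II) pain during running".
- **Abstract.** The order is reversed: "The primary outcome measure will be pain assessed using the Visual Analog Pain scale during running", while "Secondary outcomes will include pain during daily activities (usual".
- **Sample size.** The effect size is the "eta-partial square value of the group-by-time interaction for worst knee pain (0.19" in an earlier study. That is neither usual pain nor running pain.

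**The concern.** The entry rule guarantees room to improve on running pain and on one provoking task. It guarantees nothing on usual pain. Take a runner with 5/10 when running, 4/10 on resisted knee extension and 0/10 in ordinary daily life. That runner satisfies criterion III and, under the Outcomes section, enters with the primary measure already at its lowest value.

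The hypothesis is that retraining reduces pain. A participant at 0 can stay there or get worse, but cannot contribute a reduction. Each such participant pulls the mean change in the retraining arms towards zero and weakens the group-by-time contrast. A null result on usual pain would then be hard to read: it could mean that retraining does not work, or that too many participants had nothing to lose on that scale. The effect size does not settle this, because it was taken from a different pain measure.

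**Working it through.** **Step 1: eligibility against endpoint.**

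| Pain score | Entry minimum (Participants) | Role in Outcomes measures | Role in Abstract |
|---|---|---|---|
| During running | 3/10 | secondary | primary |
| One provoking task | 3/10 | not an outcome | not an outcome |
| Usual, daily activities | none | primary | secondary |

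The gap exists for the primary outcome only in the Outcomes measures column. Under the Abstract, the primary score is one that carries the minimum.

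**Step 2: reproduce the planned sample size.** Inputs from Sample size: f = 0.48, alpha 0.05, power 99%, k = 3 groups, m = 3 measurements. Correlation 0.5 between measurements and sphericity (epsilon = 1) are assumed as software defaults; the article does not state them.

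- f from partial eta squared: √(0.19/0.81) = 0.484, given as 0.48.
- Noncentrality: λ = f² × N × m/(1 − ρ).
- Degrees of freedom: (k − 1)(m − 1) = 4 and (N − k)(m − 1).
- At N = 21: λ = 0.2304 × 21 × 3/0.5 = 29.03, df 4 and 36, power 0.990. At N = 20 power is 0.986.

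The stated 21 is reproduced. The planned 30 allows for 30% loss (21/0.70 = 30), so N = 21 describes the trial with the loss allowance fully used and N = 30 the trial with no losses.

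**Step 3: illustrate the dilution.** Let q be the share of entrants with usual pain 0. Assume that they contribute no contrast between arms, that the others show the planned effect, and that the SD is unchanged. Then f becomes 0.48 × (1 − q).

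| q (assumed) | f | λ at N = 21 | Power, N = 21 | λ at N = 30 | Power, N = 30 |
|---|---|---|---|---|---|
| 0 | 0.480 | 29.03 | 0.990 | 41.47 | >0.999 |
| 20% | 0.384 | 18.58 | 0.917 | 26.54 | 0.987 |
| 30% | 0.336 | 14.22 | 0.820 | 20.32 | 0.950 |
| 40% | 0.288 | 10.45 | 0.673 | 14.93 | 0.857 |

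The article gives no value for q, so the table shows sensitivity and is not an estimate.

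**The case against.** The strongest reply is that this follows from the unresolved conflict over the primary outcome. If running pain is primary, criterion III fits it, and a secondary outcome needs no entry minimum. The entry rule could even be read as a sign that running pain was intended. That stands, and the point is conditional on it. It does not remove the point: if the conflict is settled in favour of the Outcomes section, the gap remains.

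Second, squatting, steps and kneeling are part of ordinary life, so a runner with 3/10 on one of them may well report some usual pain. This also stands. Zero usual pain may be uncommon, although resisted knee extension can serve as the qualifying task and nothing excludes a score of 0.

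Third, the 99% power target leaves a cushion. It does: with 20% at the floor, power stays above 0.90 even at N = 21.

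Several stronger readings are tempting, and the article does not support them:

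- That low scorers in general cannot improve. Only 0 is the floor; a participant at 1 can still fall to 0.
- That load-only pain with no usual pain is the typical case, or that eligibility and endpoint describe different patients. No frequency is given, and the two populations overlap.
- That an uneven split of floor participants across arms of ten would in itself invalidate the comparison. The planned model has t0 as a level of time, so arms are compared on change as well as on raw means.
- That efficacy conclusions should leave out participants who start at 0. That would conflict with the intention-to-treat rule and the exclusion of subgroup analysis in Data analysis.

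**Conclusion.** The point holds in conditional form. If usual pain is the primary outcome, criterion III lets in runners who start at the floor of that outcome, and no other section closes the gap. If running pain is primary, there is no mismatch.

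The size is unknown because the floor share is not given. In the illustration the loss of power is small at 20% and material at 40%, where power with the loss allowance fully used is about two in three. These figures rest on the assumed floor shares, the default correlation and sphericity, an unchanged SD, and an undiluted effect of f = 0.48 carried over from worst knee pain. They also assume no contrast between arms among floor participants. If such participants worsened more in the control arm than in the retraining arms, the dilution would be smaller.

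**What to change.** Reconcile the Abstract and the Outcomes measures section so that the primary outcome is the VAS item to which the entry minimum applies. There are two ways to do this.

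1. Name running pain as primary throughout. The 3/10 rule already covers it, so this costs nothing beyond the correction of the text.
2. Keep usual pain as primary and add a minimum usual-pain score to the inclusion criteria, scored at the t0 visit before allocation and not at the first contact. The investigators should choose the cut-off. The cost is one line in the criteria, since the score is already collected at t0, and a smaller recruitment pool: runners whose pain arises only under load would be excluded, although they meet the diagnostic definition in Participants.

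Merely stating that usual pain has no entry minimum would leave the problem as it is.
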